### Sample size

The VPDD from 2013-2019 has recorded an average of 147 CNVs (85 VUS, 62 pCNVs) each year. Our total potential CNV cohort for the proposed 7-year study period will be approximately 1029.

We expect losses of potential recruits due to failed contact tracing, language ineligibility, perinatal loss, and refusal of consent, and therefore conservatively estimate a final sample size of 354 women for the CNV cohort. This is based on 45% recruitment of women with fetal VUS (n=267), and 20% recruitment rate for pathogenic CNVs (n=87). This is in line with participation rates in the NICHD microarray cohort where they achieved 41%, 56% and 70% participation rates for those with pathogenic, VUS or benign/normal CMA results respectively [16]. There are 7155 potential eligible controls in the study period. We will require 5% of women with normal CMA results to be recruited to form the control cohort (n=358).

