### Statistical methods of analysis and power calculations

#### Objective 1:

The primary outcome for the 2–7-year-old group is the WPPSI-IV full IQ score. The WPPSI-IV is standardized to be normally distributed with a mean of 100 and standard deviation of 15 in the general population (variance of 30). It is therefore possible to perform the primary analysis as a single group comparison by t-test of the WPPSI-IV full IQ score in the children enrolled in this study with the population norm. A between-group analysis of the WPPSI-IV for the CNV study group and control (non-CNV) group cohorts will be done. The results from the children with VUS will be analyzed separately from those with pathogenic CNVs (pCNVs).

If 300 participants with VUS are enrolled, this will yield > 95% power and 95% confidence to detect a 3-point difference (0.2SD) in mean IQ from the norm assuming that the standard deviation is 15.

Our study cohort of women with VUS are a heterogenous group with varying indications for testing. As the presence of a fetal structural abnormality is likely to be a modifier of all assessed outcomes, a stratified analysis of the CNV cohort with and without this indication for prenatal diagnosis will be performed. An audit of the VPDD data shows that those with a fetal structural abnormality comprise two thirds of the VUS study cohort, leaving 100 to study without such an abnormality. The required sample size is therefore a minimum of 87 women without a fetal structural abnormality in each of the study and control cohorts to detect a 3-point difference in mean IQ (95% power, 95% confidence).

For the group with pCNVs, a larger difference in mean IQ is expected between those with pCNVs and those without any CNV. A minimum of 13 participants in the pCNVs cohort is required to detect a mean difference of 8 IQ points with 95% power and 95% confidence. It is expected that this analysis can be performed on the subgroup with the most common pCNV (22q11.2 deletion syndrome), which is detected prenatally in approximately 7 cases per year. If 100% progressed to live outcome, there would be at least 35 children in the cohort (born from 2013-2018) that would be able to perform the WPPSI-IV. Less than 50% would be required to be available for recruitment to meet the minimum sample size of 13.

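### The 22q11.2 subgroup is presented as able to reach a powered minimum of 13 children, but the planned 20% recruitment of pathogenic CNVs gives about 7 to 8, and 13 would not give 95% power at SD 15

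*Protocol article*

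**What the plan says.** In the statistical methods section, Objective 1, the article sets a minimum of 13 children with pathogenic CNVs to "detect a mean difference of 8 IQ points with 95% power and 95% confidence". It then expects the same analysis to be possible in the most common pathogenic CNV, 22q11.2 deletion syndrome, "which is detected prenatally in approximately 7 cases per year". Supposing that every such pregnancy ended in a live child, "there would be at least 35 children in the cohort (born from 2013-2018) that would be able to perform the WPPSI-IV", and the paragraph concludes: "Less than 50% would be required to be available for recruitment to meet the minimum sample size of 13".

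The Sample size section gives the only recruitment rate that the study plans for this class of result: "20% recruitment rate for pathogenic CNVs (n=87"). It introduces that rate after listing expected losses: families who cannot be traced, language, perinatal loss and declined consent. It also cites 41% participation among women with pathogenic results in the US cohort. Neither section gives a separate rate for 22q11.2.

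Objective 1 describes the IQ scale as having a "mean of 100 and standard deviation of 15 in the general population (variance of 30").

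**The concern.** The feasibility statement and the recruitment plan use different rates for the same children. One needs well over a third of the 22q11.2 cases; the other budgets a fifth of all pathogenic CNVs. The statement never mentions the 20%, so a reader of Objective 1 alone would take the subgroup analysis as comfortably achievable.

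The target of 13 is also unsafe, because an SD of 15 means a variance of 225, not 30.

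The 22q11.2 group is the only individual CNV for which the plan states a powered minimum on the primary outcome. If it is analysed with 7 or 8 children under a stated 95% power, a non-significant result could be read as evidence of no important IQ deficit when the data could not show one either way.

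**Working it through.** **Inputs.** From Objective 1: difference 8 points, power 95%, confidence 95% (taken as two-sided α = 0.05), SD 15, variance printed as 30, about 7 cases of 22q11.2 per year, at least 35 children, minimum 13. From Sample size: 62 pathogenic CNVs per year, 7 years, 20% recruitment, 358 controls, 41% participation in the US cohort.

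**1. What the 20% applies to.** 62 × 7 = 434 recorded pathogenic CNVs; 434 × 0.20 = 86.8, the stated 87. So 20% is an all-in yield from recorded prenatal results, net of losses.

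**2. Rate needed for 13.** 13/35 = 37%. If all six birth years 2013–2018 count, 7 × 6 = 42 and 13/42 = 31%. Both are below 50%, so the quoted sentence is true as arithmetic. Both are 1.5 to 1.9 times the planned 20%.

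**3. Expected number at the planned rate.** 35 × 0.20 = 7.0; 42 × 0.20 = 8.4. Treating recruitment as binomial at 20%, P(at least 13) is 1.4% from 35 and 6.2% from 42.

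**4. Where 13 comes from.** For two equal groups, n per group = 2σ²(1.960 + 1.645)²/δ².
- σ² = 30, δ = 8: 2 × 30 × 13.0/64 = 12.2, so 13. The stated figure reproduces.
- σ² = 30, δ = 3: 2 × 30 × 13.0/9 = 86.6, so 87. This is the article's other minimum, which confirms that 30 was the variance used.
- σ² = 225, δ = 8: 2 × 225 × 13.0/64 = 91.4, so 92 per group. A one-sample test against the norm needs half of this, 46.

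**5. Power at SD 15 against 358 controls.** SE = 15√(1/n + 1/358); power = Φ(8/SE − 1.960).

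| Children with the CNV | SE | 8/SE | Power |
|---|---|---|---|
| 7 | 5.73 | 1.40 | 29% |
| 8 | 5.36 | 1.49 | 32% |
| 13 | 4.24 | 1.89 | 47% |
| 35 | 2.66 | 3.01 | 85% |
| 42 | 2.45 | 3.27 | 90% |
| 53 | 2.21 | 3.62 | 95% |
| 87 (all pathogenic) | 1.79 | 4.46 | 99% |

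The smallest number that reaches 95% is 53.

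**6. All pathogenic CNVs, WPPSI-IV age only.** The article does not give this number. Assuming that five of the seven years contribute, 87 × 5/7 ≈ 62 and 358 × 5/7 ≈ 256, and power is about 96%.

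**7. Precision of a 22q11.2 mean.** The 95% CI half-width is t × 15/√n: 2.447 × 15/√7 = 13.9 for 7 children, and 2.365 × 15/√8 = 12.5 for 8. Both exceed the 8 points sought.

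**The case against.** The best defence is that the feasibility sentence is conditional on full live outcome, and under that condition 20% is no longer the matching rate because it already carries perinatal loss. This stands. A reader might infer that only 7 or 8 children would be recruited even if every pregnancy were liveborn, or that 7 or 8 is a count before terminations. The documents support neither: 7 to 8 is what remains after losses. With every child liveborn and the US cohort's 41%, 35 × 0.41 = 14.4 and 42 × 0.41 = 17.2, both above 13. But that takes full live outcome together with about double the planned rate, and the Sample size section budgets for neither.

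A reader might also infer that 35 is a miscount of 42. That is not shown. The text says at least 35 and counts only children able to take the WPPSI-IV. Table 2 caps the older cohort at 7 years 7 months at enrolment, and the article was submitted in May 2021, so some children born in 2013 could already be too old. The conclusion is the same for either count.

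Much of the fall from 95% power is due to the variance figure, not recruitment: even 13 children give only 47%. The two faults are therefore kept apart here. Recruitment explains the shortfall against 13; the variance explains why 13 was too small.

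Finally, the minimum is set for the pathogenic group as a whole, where 87 are planned, and the section on poor recruitment foresees pooling with the US cohort. The first point limits the damage to the subgroup. The second is a general fallback and does not support a power stated for this study's own sample.

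**Conclusion.** The concern holds for the 22q11.2 subgroup. The feasibility statement needs 31–37% of cases where the plan budgets 20%, so about 7 to 8 children are expected after losses against a stated minimum of 13. Separately, at SD 15 no level of recruitment from 35 to 42 children reaches the stated 95% power for 8 points against 358 controls; the expected 7 to 8 give 29–32%.

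This rests on three assumptions: the general pathogenic-CNV rate applies to 22q11.2, since no other is given; the SD is 15 in both groups; and all 358 controls contribute IQ scores, which favours the plan. A true deficit larger than 8 points would be easier to detect, but the stated power is for 8.

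The fault is an inconsistency between two planning assumptions, together with a wrong variance. It is not a slip in the quoted percentage. It does not undermine the comparison of all pathogenic CNVs with controls.

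**What to change.** In Objective 1:
- Remove the statement that the 22q11.2 subgroup can meet a powered minimum, and correct the variance to 225 with the minimum of 13 recalculated.
- State all pathogenic CNVs versus controls as the powered contrast: 87 planned, about 99% power for 8 points at SD 15, and somewhat lower (about 96% on the five-sevenths assumption) once restricted to children of WPPSI-IV age.
- Report 22q11.2 descriptively, as a mean with 95% CI. Give the expected number as about 7 to 8 after losses at the planned 20% rate, and the expected half-width as about 12.5 to 14 points.
- If the investigators expect a higher rate for 22q11.2, state it and its basis, and reconcile it with the Sample size section.

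The cost is wording only. Recruitment, assessments and the main pathogenic-CNV comparison are unchanged; what is lost is a subgroup power claim that the planned numbers cannot support.

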#### Secondary outcomes

Vineland-II Adaptive Behavior Scale (VABS) scores, adjusted z-scores for growth, overall frequency of medical problems. As for the primary outcome, secondary outcomes will also be analyzed according to their subgroups (pCNVs and VUS). Multivariable logistic (for binary outcomes) or linear (for continuous outcomes) regression analysis will be performed to account for modifiers and confounders, such as maternal age, parental education level, gestational age at birth.

#### For the 12–24-month-old group, the ASQ-3 and ASQ:SE-2 scores are the primary outcomes

Scores for individual items are summed to give an overall continuous score for each of the domains in the ASQ-3 and ASQ:SE-2. In addition to using scores as continuous outcomes, we will categorize the scores according to the recommended scores for typical development, need for monitoring, and need for further assessment. We will collapse these three categories into a binary variable (those with typical development vs those with a need for monitoring or further assessment [i.e., potential atypical or delayed development]). The differences in those with typical and ‘atypical’ scores will be compared among the CNV subgroup using chi-squared test for proportions or Fisher’s exact test as appropriate.

#### Objective 2

The primary outcome will be the BITSEA score. We will analyze the data according to the subgroup of CNV result (pCNV, VUS) compared with controls, stratified by age. The secondary outcomes will be the Maternal Postnatal Attachment Questionnaire (MPAS), Vulnerable Child Scale (VCS), Profile of Mood States (POMS), and the Parent Sense of Competence Scale (PSOC). For the secondary outcomes, we will compare group differences in responses using mixed effect regression models. We will report mean values for the parent report of child behavior, parenting competence, attachment, perceived child vulnerability and parent mood. Parent gender, country of birth, education, employment status, and child sex will be adjusted as covariates.

#### Objective 3

We will compare the classifications given at the time of issue of the prenatal report and the current classifications in 2020-21 according to the issuing laboratory’s protocols. The proportion of pCNVs, VUS and benign variants will be compared between the prenatal and 2-year postnatal classifications using chi-squared test for proportions.

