## Background

Congenital anomalies, of which one third are chromosomal in origin, are the leading cause of perinatal death in Australia [1]. Prenatal screening for fetal chromosomal conditions is thus an important component of care for the 300,000 women who give birth in Australia each year. National guidelines recommend that voluntary screening, and the option of follow-up prenatal diagnosis, be provided to all pregnant women [2]. In 2019, Victoria recorded 409 prenatal diagnoses of major chromosome conditions, in a state population with 76,000 births per year (1 in 186 births) [3].

Over the past decade, technological advances have revolutionized genetic testing at every stage of reproduction [4]. Classical cytogenetics has been superseded by chromosomal microarray (CMA) as the gold standard for chromosomal assessment [5]. CMA interrogates the genome at a higher resolution than conventional karyotyping, allowing previously undetected submicroscopic copy number variants (CNVs) to be detected. A National Institute of Child Health and Human Development (NICHD) multicenter trial in the United States (US) provided the first large-scale report on the use of CMA for fetal chromosome analysis [6]. This landmark trial compared the accuracy of prenatal CMA to that of standard karyotyping and found that 5.8% of pregnancies with a fetal structural anomaly and a normal karyotype had a clinically significant CNV detected. Professional societies now recommend the use of prenatal CMA, particularly for the investigation of fetal structural anomalies [2, 7]. This has rapidly transitioned to being the ‘default’ investigation for any prenatal diagnostic test and accordingly in Victoria, the annual proportion of prenatal diagnoses utilizing CMA has exceeded 80% since 2015 [3].

The genomic imbalances detected by CMA include pathogenic CNVs (pCNVs) that are associated with well-described syndromes such as the 22q11.2 deletion syndrome and Prader-Willi / Angelman syndromes. However, with the ability of CMA to detect smaller genomic imbalances than conventional karyotype, comes a correspondingly higher detection rate of uncertain findings [8]. These variants of uncertain (or unknown) significance (VUS) are CNVs that have a variable amount of evidence available to assess their pathogenicity. Parental testing is often required to assist in interpretation of fetal VUS.

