Fetal VUS present special clinical and ethical challenges compared with the pediatric setting [9]. VUS are reported in 5% of prenatal samples in Victoria, resulting in almost 100 women each year being informed that their unborn baby has an uncertain diagnosis [10]. These VUS include CNVs that may predispose to developmental disability or neuropsychiatric illness, but which are highly variable and unpredictable in effect (“neurosusceptibility CNVs”) [11]. Interpretation of uncertain variants during pregnancy requires more caution because where there is no apparent fetal phenotype, this information may bring more harms than benefits. There is currently no guidance for structured assessment and follow-up for these children after birth. Furthermore, our understanding of the clinical significance of variants is continuously evolving, and classification of CNVs may change over time without patients being notified of updated information.

Long-term outcomes of prenatally-ascertained CNVs are needed. To our knowledge, worldwide, there are only two cohort studies in progress investigating the postnatal outcomes of prenatal CNVs detected on CMA – the NICHD sponsored cohort from the United States [6] and the Belgium MicroArray Prenatal (BEMAPRE) consortium [12]. Generating new knowledge on long-term outcomes of fetal genomic variants will have a positive health impact by supporting (i) evidence-based pre- and postnatal care, and (ii) mitigating the negative consequences of conveying genomic uncertainty during pregnancy.

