## Methods/Design

### Aims

The PALM cohort study will establish and follow-up a cohort of mother-child pairs who had a prenatal diagnosis of a CNV from 2013-2019 (inclusive) in the Australian state of Victoria. Victoria has approximately 78,000 births per year and a median maternal age of 31.5 years [13]. Approximately 2-3% of all pregnant women undergo prenatal diagnosis per year [14].

The study aims are to:
Compare the developmental, social-emotional and health status of children with a prenatal diagnosis of a prenatal CNV with those children with no CNV detected on CMA.Measure the impact of a prenatal diagnosis of a CNV on maternal perceptions of child health, behavior, and development.Determine the proportion of CNV ascertained prenatally that are reclassified from unknown or uncertain to benign or pathogenic after two or more years using contemporaneous curation resources.

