### Women’s experience of prenatal VUS

While most children with VUS are expected to have normal outcomes, the possibility of an increased risk of developmental disorder can result in parental anxiety, termination of healthy pregnancies, “hypervigilant” parenting styles, and increased utilization of medical services [36]. A prenatal diagnosis of a VUS may also alter early parental perceptions of the competency of the child [16]. Our study will be able to determine whether there are any such ‘harms’ associated with the disclosure of VUS, and enable us to develop strategies to mitigate these negative effects.

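### Objective 2 is worded as the impact of the diagnosis, but a mother who transmitted the CNV may answer differently because of her own genotype, and inheritance is not in the stated adjustment

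*Protocol article*

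**What the plan says.** The second aim, under Aims, is causal in wording: "Measure the impact of a prenatal diagnosis of a CNV on maternal perceptions of child health, behavior, and development". The Discussion, under Women's experience of prenatal VUS, goes further: "Our study will be able to determine whether there are any such ‘harms’ associated with the disclosure of VUS".

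The Objective 2 text in the statistical methods names BITSEA as primary outcome and continues: "We will analyze the data according to the subgroup of CNV result (pCNV, VUS) compared with controls, stratified by age". Four maternal scales (MPAS, VCS, POMS and PSOC) are named as secondary outcomes. Group differences on these are to be estimated with mixed-effects regression, and the adjustment set is fixed: "Parent gender, country of birth, education, employment status, and child sex will be adjusted as covariates". Table 2 lists all five instruments (BITSEA, MPAS, VCS, POMS, PSOC) as completed by the parent.

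Two statements in the Background bear on the mother's own genotype. On the variants: "These VUS include CNVs that may predispose to developmental disability or neuropsychiatric illness, but which are highly variable and unpredictable in effect". On parental testing: "Parental testing is often required to assist in interpretation of fetal VUS". Under Inclusion criteria, the consenting parent is the biological mother.

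**The concern.** When a CNV is maternally inherited, the mother's genotype comes before both sides of the comparison. It is the reason her fetus has the CNV, and so the reason she received the diagnosis. If the variant is one of those the Background describes, it may also affect her mood, her sense of competence, her attachment, and how she rates her child's vulnerability and behaviour. Controls have no reported fetal CNV, so this transmission route exists only in the CNV groups. De novo and paternally inherited CNVs do not carry it.

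A VUS-control difference on these scales could therefore arise partly from carrier mothers and be read as an effect of disclosure. This matters because the article says the results may inform the value of revealing VUS during pregnancy and help develop strategies against the harms of doing so.

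**Working it through.** **1. Where inheritance could enter the plan**

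| Place in the article | What is named | Inheritance named? |
|---|---|---|
| Study population (matching) | fetal sex, trimester, maternal age group, calendar year | no |
| Screening and baseline health assessment | demographics, pregnancy outcomes, state and trait anxiety, health literacy, health care use | no |
| Table 2 (instruments, laboratory reanalysis) | scales, child assessments, software and databases | no |
| Objective 1 stratification | fetal structural abnormality; VUS and pCNV separately | no |
| Objective 1 secondary outcomes | open list of modifiers and confounders | not named, but the list is open |
| Objective 2 | CNV class, age strata; five covariates for the secondary scales | no, and the list is closed |

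Parental genotype appears only in the Background sentence on parental testing.

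**2. Figures available**

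The article gives no effect size, power or sample size specific to Objective 2, so there is no stated figure to reproduce. The planned group sizes in the Sample size section follow from its own rates:
- VUS: 85 × 7 × 0.45 = 267.75 (stated as 267).
- Controls: 7155 × 0.05 = 357.75 (stated as 358).

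**3. Precision of the VUS-control contrast**

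This assumes everyone recruited is analysed, with no covariates or age strata, a common SD, a normal approximation and two-sided α = 0.05 (the α is also assumed).
- SE = √(1/267 + 1/358) = 0.081 SD.
- Difference detectable at 80% power = (1.960 + 0.842) × 0.081 = 0.23 SD.

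**4. Bias if the diagnosis has no effect**

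Bias = m × p × d, where
- m is the share of VUS that are maternally inherited,
- p is the share of those variants that affect the mother,
- d is the effect on her score in SD units.

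None of the three is in the documents. I assume m = 0.20 to 0.40 and d = 0.3 to 0.5, and vary p because the Background attributes the predisposition to only some VUS. The chance of a significant result is Φ(bias/SE − 1.96) + Φ(−bias/SE − 1.96).

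| p (assumed) | Low bias (m = 0.20, d = 0.3) | Chance | High bias (m = 0.40, d = 0.5) | Chance |
|---|---|---|---|---|
| 0.25 | 0.015 SD | 5.4% | 0.05 SD | 9.5% |
| 0.50 | 0.03 SD | 6.6% | 0.10 SD | 23.5% |
| 1.00 | 0.06 SD | 11.5% | 0.20 SD | 69.6% |

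The range runs from almost nothing to a bias close to the difference the study could detect. The documents do not say where in it the truth lies.

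**The case against.** **The article is condensed.** An extra field and a sensitivity analysis are often left to a full protocol or SAP. That is fair for the sensitivity analysis itself. But the article fixes the Objective 2 contrast and closes its covariate list while using causal wording, and a variable that is never collected cannot be used later. It would still be too much to say that inheritance is excluded from every analysis: the Objective 1 confounder list is open.

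**The size rests on assumption.** This stands. The Background says only that VUS include such variants and that their effects are unpredictable. A reader might take the 70% as the expected error rate. The documents do not support that, because it needs the top of both assumed ranges and an effect from every maternally inherited VUS.

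**The covariates are not blind to the path.** This stands in part. Education and employment status may carry some of a carrier mother's disadvantage. Anxiety and PHQ-8 are also collected, but they are not named as Objective 2 covariates. Measured after disclosure, they could not cleanly stand in for genotype.

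**The primary outcome is a child measure.** The quoted contrast concerns BITSEA, so there the path needs a further step: the mother's variant must change how she rates her child. The route is more direct for POMS and PSOC.

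**Leaving out carriers changes the question.** This also stands. Learning that she passed on the variant may be part of what the diagnosis does to a mother. De novo and inherited CNVs may also differ in their effect on the child. A gap between the two analyses would therefore not prove confounding, and a rule requiring them to agree has no defined criterion and could discard a real effect.

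**Availability of the data.** The Background says testing is often required, not that results are held in a retrievable field. Some inheritance will be unknown.

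**Conclusion.** The concern holds as a plausible, unaddressed confounding path of unknown size. It rests on the article's own statements: the causal aim, the biological mother as respondent, the neuropsychiatric predisposition of some VUS, and a closed adjustment set without inheritance. Under the assumptions shown, the spurious VUS-control difference is 0.015 to 0.20 SD and the false-positive chance about 5% to 70%. These figures show sensitivity to the assumptions and do not estimate the bias.

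A reader might infer that any difference found under Objective 2 would be an artefact of maternal genotype, or that the objective cannot be answered. The documents do not support either reading. The path concerns only maternally inherited variants, and among VUS only those with a neuropsychiatric effect; the existing covariates may absorb part of it. What the plan lacks is a way to see how much of a difference depends on these mothers, and wording that allows for them.

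**What to change.** 1. Where parental testing was done, record inheritance (maternal, paternal, de novo, unknown) from existing laboratory or health records. Participants already give permission for health-record data, and the laboratories already handle each case for pre-screening and reanalysis.
2. Prespecify one sensitivity analysis that repeats each Objective 2 contrast without known maternally inherited CNVs. Report its estimates and confidence intervals beside the main ones, with no rule that the two must agree.
3. Word the main result as an association with CNV result. State that maternal carrier status may contribute, and that learning of carrier status may itself be part of the effect of the diagnosis.

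**Cost.** One data field, one additional analysis and a change of wording. The subset is smaller and may be selected, since not every family was tested, and mothers of unknown status stay in it, so some of the path may remain. If an assumed 20% to 40% of the 267 VUS were left out, about 214 to 160 would remain. The SE would rise from 0.081 to √(1/214 + 1/358) = 0.086 or √(1/160 + 1/358) = 0.095 SD.
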